
#### Phase 2

The goal of Phase 2 is to enroll approximately 140 patients across the three enrolling site EDs to establish current clinical practice patterns with regard to obtaining head CTs for patients who meet the study's inclusion/exclusion criteria. Prior to initiating patient enrollment, site principal investigators will brief emergency medicine and trauma faculty about the research study, the POC whole blood TBI test, and how to interpret the test results. The intent of this phase is to establish early stakeholder engagement and obtain feedback from frontline clinicians that will inform development of the implementation blueprint in Phase 4.

Timeline of participant outcome assessments can be viewed in Table 1. The primary endpoint of this phase is the rate of head CTs completed in enrolled patients. The secondary endpoint of this phase is the rate of head CTs completed in enrolled patients with negative POC whole blood test results. These primary and secondary endpoints were selected to match the FDA's framing of clinical benefit and to be directly comparable to ongoing and completed studies evaluating utility of blood biomarkers for CT utilization in the ED (6, 17–19). Additional secondary outcomes include ED length of stay (in minutes), return to ED for the same injury within 2 weeks of first ED presentation (yes/no), Military Acute Concussion Evaluation-2 (MACE-2) results, Neurobehavioral Symptom Inventory (NSI), and two customized surveys about knowledge of mTBI and knowledge of the effects of radiation exposure in healthcare settings. ED length of stay can be extracted from the electronic medical record by research personnel, as presentation and discharge from the ED are timestamped. The MACE-2 is a multimodal tool which assesses clinical signs of TBI, incident description, signs, symptoms, medical history, a brief cognitive exam, neurological exam, and modified Vestibular Ocular Motor Screening (VOMS). The MACE-2 takes approximately 15 min to complete. The NSI is a 22-item scale of TBI symptoms since the time of injury.

**Table 1 T1:** Timeline of patient participant outcome assessments.

Outcome	Enrollment	Two-week follow-up
Military Acute Concussion Evaluation—2	X	
Neurobehavioral Symptom Inventory	X	X
Traumatic brain injury knowledge	X	
Radiation exposure knowledge	X	
Quality of Life After Brain Injury Overall Scale		X
Follow-up care survey		X

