### Statistical analysis

Normality will be assessed for all outcomes, and appropriate transformations will be made to ensure that statistical assumptions are met prior to conducting all analyses. Statistical significance for these evaluations will be set at *p* < 0.05, and Bonferroni corrections will be applied to all analyses for multiple comparisons.

#### Phase 1

For Phase 1, descriptive statistics will be calculated for POC whole blood TBI test results, including the rates of elevated vs. non-elevated values, rates of CT scans ordered, and rates of return ED visits for the same injury within 2 weeks in the first group of 140 ED patient participants. Whether or not the patient returned will be self-reported at the 2-week follow-up survey sent to the participants. ED length of stay (in minutes) will be compared between patients who only received the POC whole blood TBI test and those who received the POC whole blood TBI test and a head CT scan using an analysis of covariance model, including enrollment site as a covariate. This analysis will be conducted only for participants with a negative POC whole blood TBI test to control for clinical severity of the injury. An exploratory analysis using receiver operating characteristic area under the curve (AUC) will be conducted to differentiate patients who return to the ED for evaluation of the same injury within 2 weeks from those who do not, using whole blood GFAP and UCH-L1 as predictors. Approximately 5% of patients diagnosed with TBI and GCS scores of 13–15 in the ED return to the ED within 72 h of discharge for TBI evaluation (27). The expected event rate would yield seven returns to the ED for the Phase 2 cohort of *n* = 140, which is lower than the standard expectation of 10 events per predictor. Statistical significance for these evaluations will be set to *p* < 0.05.

#### Phase 2

For Phase 2, descriptive statistics for all determinant measures will be calculated. Items from the Mi-PARIHS will be plotted as originally described for visual inspection of the weakest domains. These statistics will be calculated by site and by stakeholder type to facilitate presentation to the CAB and to inform development of the implementation blueprint.

Phase 3 will not have a corresponding statistical analysis because it is entirely dedicated to the development of the site-specific blueprints.

#### Phase 4

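### ED return and its exploratory AUC are not limited to patients discharged from the index ED visit, and a per-discharge rate is applied to all 140 enrolled patients

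*Protocol article*

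**What the plan says.** The Phase 2 part of the Methods lists among the additional secondary outcomes "return to ED for the same injury within 2 weeks of first ED presentation (yes/no". The Statistical analysis section, under its Phase 1 heading (which describes the first 140 patients), gives the source of the data: "Whether or not the patient returned will be self-reported at the 2-week follow-up survey sent to the participants". It then plans an exploratory ROC AUC with GFAP and UCH-L1 as predictors "to differentiate patients who return to the ED for evaluation of the same injury within 2 weeks from those who do not". The same analysis is repeated under Phase 4, Secondary outcome comparison.

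The planning rate is about 5% of patients who "return to the ED within 72 h of discharge for TBI evaluation". From it the protocol concludes: "The expected event rate would yield seven returns to the ED for the Phase 2 cohort" of 140, and it acknowledges that this falls short of 10 events per predictor.

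The Eligibility criteria do not exclude patients who are admitted, and no section restricts the return outcome or its AUC by disposition.

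**The concern.** A yes/no outcome that starts at first presentation, in everyone enrolled, treats all patients as equally able to return. Patients admitted from the ED are not: while they are in hospital they cannot return. If asked at two weeks, an admitted patient will usually answer no and so becomes a control in the ROC analysis.

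This misplacement is probably related to the predictors. The Background says that values below both cutoffs rule out the need for a head CT, so higher values go with intracranial lesions. That patients with lesions are more often admitted is a reasonable inference, though the article does not state it. Controls with high markers and little opportunity for the event would lower the apparent discrimination.

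The planning figure has a related mismatch: a rate among discharged patients is multiplied by a cohort that may include admitted ones.

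At stake is a named secondary aim of Phase 2, the predictive utility of the test for ED revisits. The closing section on anticipated impact presents this as the first known evidence of its kind.

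**Working it through.** **Inputs from the protocol.** Phase 2 cohort of 140; return rate of about 5% within 72 h of discharge; seven expected returns.

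**Inputs assumed.** The share admitted is not given; 5% to 30% is used here. The true AUC among discharged patients is not given; 0.65 and 0.70 serve as illustrations.

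**1. The plan's own figure.** 0.05 × 140 = 7.0. It reproduces, but only if all 140 patients are discharged.

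**2. Expected returns on the discharged denominator.** Expected returns = 0.05 × 140 × (1 − share admitted).

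| Share admitted (assumed) | Discharged | Expected returns |
|---|---|---|
| 0% | 140 | 7.0 |
| 5% | 133 | 6.65 |
| 10% | 126 | 6.3 |
| 20% | 112 | 5.6 |
| 30% | 98 | 4.9 |

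This holds the 72-hour rate fixed. The outcome window is 2 weeks, so the count could be higher, but the protocol gives no 2-week rate.

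**3. Upper bound on the AUC shift.** Suppose there are 7 returners, all discharged, and 140 − 7 = 133 non-returners, of whom *a* were admitted. If every admitted patient ranks above every returner, those pairs contribute nothing:

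AUC in all enrolled = AUC in discharged × (133 − *a*)/133

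- 5% admitted, *a* = 7: 0.65 × 126/133 = 0.616
- 10% admitted, *a* = 14: 0.65 × 119/133 = 0.582

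The shifts are 0.034 and 0.068.

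**4. A milder model.** Take normally distributed markers of equal variance, with admitted patients 1.0 to 1.5 SD above discharged non-returners and the 5% return rate applied to discharged patients. The all-enrolled AUC is then the average of the AUC against discharged non-returners and the AUC against admitted patients, weighted by their numbers. A true 0.70 becomes:

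- 10% admitted: 0.671 to 0.658
- 20% admitted: 0.643 to 0.616
- 30% admitted: 0.615 to 0.574

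The direction is the same. The size depends wholly on the assumed share and separation.

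**5. Sampling error for comparison.** Hanley–McNeil variance with A = 0.65, 7 events and 133 non-events: A/(2 − A) = 0.4815; 2A²/(1 + A) = 0.5121; A² = 0.4225.

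Variance = [0.2275 + 6 × (0.4815 − 0.4225) + 132 × (0.5121 − 0.4225)]/(7 × 133) ≈ 12.41/931 = 0.0133

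The SE is about 0.115 and the 95% half-width about 0.23. The bounding shifts of 0.034 and 0.068 lie well inside this.

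**The case against.** **No rule codes admitted patients as non-returners, and an article may leave such handling to the full protocol or SAP.** It is true that no such rule is written. But the clock, the contrast and the expected count are written, and following them gives this result.

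**The bounding calculation is a worst case.** This stands. It assumes that no admitted patient returns, although a short stay leaves much of the 2 weeks at risk. It also assumes that admitted patients outrank all returners, although in the pilot only about one in five patients tested negative, so elevated values were common.

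**The analysis is exploratory and already conceded to be short of events.** This stands and limits the severity. Moving from 7 to 6.3 expected returns does not change that concession. It does not remove the bias either.

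**Restricting to discharged patients conditions on something that happens after the test.** This stands. Clinicians are briefed on interpreting the results, so disposition may be influenced by them. It is the reason to keep the all-enrolled AUC as a sensitivity analysis.

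**Two stronger readings are not supported.**

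- A reader might infer that the AUC could be turned into an inverse association. In the bounding formula this needs, for example, 20% admitted and a true AUC of 0.60: 0.60 × 105/133 = 0.474. The Background puts positive CTs below 10%, and lower still in mild TBI, and significant polytrauma is excluded. Nothing supports 20% admitted with top-ranked markers.
- A reader might infer that ED length of stay is biased in the same way by boarding of admitted patients. For the comparison of test only with test plus CT, the protocol says: "This analysis will be conducted only for participants with a negative POC whole blood TBI test to control for clinical severity of the injury". Its later sentence on overall cohorts speaks of rates and does not clearly set a length-of-stay contrast. Boarding is also part of true ED stay. It biases a comparison only if admission share or boarding time differs between the groups compared, and the article does not show that it does.

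**Conclusion.** The concern holds for ED return only, as a minor point. The outcome and its AUC include patients with reduced time at risk among the non-returners, and the expected count applies a per-discharge rate to everyone enrolled. With an assumed 10% to 30% admitted, that count is 6.3 to 4.9 instead of 7.

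The AUC would tend to be pulled down, provided that admitted patients do have higher markers. How far cannot be computed without an admission share. The fall from 0.65 to 0.62 or 0.58 at 5% or 10% admitted is an upper bound, and small against the sampling error with about seven events. The head CT endpoints and the sample size are not touched.

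**What to change.** - Record ED disposition for every patient. Research personnel already take ED times from the electronic record, "as presentation and discharge from the ED are timestamped"; the article does not say that disposition is extracted as well.
- Define ED return, and run the AUC, among patients discharged from the index ED visit, with the 2-week clock starting at ED discharge.
- Report admitted patients separately, and give the all-enrolled AUC as a sensitivity analysis.
- Restate the expected number of returns on the discharged denominator.
- Leave the definition of length of stay as it is. At most, report it by disposition if the overall cohorts are compared between phases.

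The cost is one extra extracted field, a change of endpoint wording and a slightly smaller denominator for the return analysis.

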### Patient participants

The study team will identify potential participants with suspected TBI according to approved local processes. Eligibility criteria may be reviewed through electronic medical records and patient interviews. Eligible patients may be approached to discuss participation. Enrolled patients will be asked to complete a brief battery of questionnaires about their injury and knowledge about concussion and radiation.

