### Funding and ethics approval

This study received the Health Sciences Research Award from the Congressionally Directed Medical Research Program's Traumatic Brain Injury and Psychological Health Research Portfolio (No. HT94252510275). The study received ethical approval from the University of Pittsburgh's Institutional Review Board on 24 November 2025 (No. STUDY25010137) in accordance with the Declaration of Helsinki. The study's protocol was registered on ClinicalTrials.gov on 4 February 2026 (No. NCT07373509) prior to the initiation of study procedures. All human subjects will provide informed consent prior to completing study procedures.

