### Whole blood TBI test

POC testing will be conducted using the iSTAT Alinity whole blood TBI cartridge and point-of-care analyzer (Abbott Laboratories, Chicago, IL, USA). The POC whole blood TBI test will be performed at each enrolling site within the FDA-approved indication and will be operated by appropriately trained personnel (6). Quality control and product validation will be performed according to manufacturer and CLIA requirements. A single venipuncture will be performed in the ED to obtain ∼3 mL of whole blood to be used for testing.

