Patients will also receive a series of surveys to complete remotely approximately 2 weeks after the initial visit. Patients will complete the NSI, the Quality of Life After Brain Injury Overall Scale (QOLIBRI-OS), and a brief custom survey about follow-up clinical care. The QOLIBRI-OS is a 6-item tool evaluating how a participant's brain injury has impacted their health-related quality of life.

#### Phase 3

The goal of Phase 3 is to design and deploy site-specific implementation blueprints based on determinants of use identified in Phase 1 and stakeholder feedback and practice patterns from Phase 2. The i-PARIHS framework will be used to select implementation strategies that will address identified facilitators and barriers from the Mi-PARIHS assessment in Phase 1.

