##### Secondary outcome comparison

ED length of stay (in minutes) will be compared between patients who only received the POC whole blood TBI test and those who received the POC whole blood TBI test and a head CT scan using an analysis of covariance model including enrollment site as a covariate. This analysis will be conducted only for participants with a negative POC whole blood TBI test to control for clinical severity of the injury. Differences in these rates following implementation will be evaluated using the same approach (both for the overall cohorts and those with a negative POC whole blood TBI test only). An exploratory receiver operating characteristic AUC analysis will be conducted to differentiate patients who return to the ED for evaluation of the same injury within 2 weeks from those who do not, using whole blood GFAP and UCH-L1 as predictors.

To evaluate the effect of the implementation blueprint on perspectives regarding determinants and implementation outcomes, Mi-PARIHS domain scores will be compared pre- and post-implementation using repeated measures general linear model, including site as a covariate. Secondary comparisons will be made for implementation outcomes (e.g., AIM, FIM, and DCS).

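### ED length of stay includes consent and the enrollment assessments, which may attenuate the time saving in patients who have no head CT

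*Protocol article*

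**What the plan says.** The Phase 2 section of the Methods names ED length of stay as a secondary outcome and fixes its clock: "ED length of stay can be extracted from the electronic medical record by research personnel, as presentation and discharge from the ED are timestamped".

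The protocol article then places study activity inside that interval:

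- Funding and ethics approval: "All human subjects will provide informed consent prior to completing study procedures".
- Whole blood TBI test: "A single venipuncture will be performed in the ED". Consent therefore comes before a draw that takes place in the ED.
- Patient participants: "Enrolled patients will be asked to complete a brief battery of questionnaires about their injury and knowledge about concussion and radiation".
- Table 1 puts the MACE-2, the NSI and the two knowledge surveys at enrollment. The text gives one duration: "The MACE-2 takes approximately 15 min to complete".
- The only assessments described as remote are the later ones: "Patients will also receive a series of surveys to complete remotely approximately 2 weeks after the initial visit".

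The section on the secondary outcome comparison sets two groups against each other: "ED length of stay (in minutes) will be compared between patients who only received the POC whole blood TBI test and those who received". The second group had a CT as well as the test, and the model is an analysis of covariance with site as covariate. It is restricted: "This analysis will be conducted only for participants with a negative POC whole blood TBI test to control for clinical severity of the injury". The same section goes on to compare the phases, in the overall cohorts and in the test-negative patients. I read that as covering length of stay.

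**The concern.** The outcome counts research minutes as well as care minutes. If those minutes lengthened every stay equally, the comparison would be unaffected. There is reason to think they may not.

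The first exclusion criterion removes patients whose provider sees no need for a head CT, so the CT pathway can already be running while consent and assessments take place. A patient who goes on to CT has that wait in which to do them. A test-negative patient who skips CT may be ready to leave soon after a 15-minute assay, and the same tasks may then keep that patient in the ED. Consent also precedes the draw, so it can delay the result that would allow CT to be avoided.

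At stake is a named secondary outcome. The Discussion presents time spent in the ED as a study goal and as evidence likely to influence uptake. The measured difference may understate the saving, and the minutes reported would not be those of routine care. This is separate from the question of which patients are chosen for CT: it would remain if CT were allocated at random, and adjustment for site does not remove it.

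**Working it through.** **The plan's own figures.** The article gives no target difference, standard deviation or sample size for length of stay. Its one sample size, 140 per phase, is for the CT rate (95% vs 75%, two-sided alpha 0.01, power 0.99). Exact two-sided Fisher power at 140 per phase is 0.988, so it is close to reproduced, but it has no bearing on this point.

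**Inputs**

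- MACE-2: 15 min (Methods, Phase 2).
- Consent, NSI and two knowledge surveys: no duration given. Assumption: 10 to 30 min together.
- Assay time: 15 min (Background).
- Test result ahead of CT result: 2.5 h = 150 min in the pilot with the plasma test, plus 45 min expected from whole blood (Preliminary work), so 150 + 45 = 195 min.
- CT rates: 95% in Phase 2, 75% in Phase 4 (Power analysis).

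**Research time per patient.** R = 15 + (10 to 30) = 25 to 45 min.

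**Effect on the CT versus no-CT difference.** Let a(CT) and a(no CT) be the shares of R that fit into waits the patient would have had anyway. Then

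understatement = R × [a(CT) − a(no CT)].

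| a(CT) | a(no CT) | R = 25 | R = 45 |
|---|---|---|---|
| equal | equal | 0 min | 0 min |
| 1 | 0.5 | 12.5 min | 22.5 min |
| 1 | 0 | 25 min | 45 min |

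The first row covers tasks that fit existing waits in both groups and tasks that add equally to both. The last row is the extreme. The range of 0 to 45 min assumes that CT patients absorb at least as much as no-CT patients. Counting the MACE-2 alone, the maximum is 15 min.

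**Effect on the overall phase comparison.** The no-CT share rises from 5% to 25%, that is by 0.20. At the extreme, the understatement is 0.20 × 25 = 5 min to 0.20 × 45 = 9 min. In the test-negative subset the no-CT share may change by more, but the article gives no planned CT rate for that subset.

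**Against the only CT comparison available.** 25/195 = 13% and 45/150 = 30%, again at the extreme. These percentages are orientation only: 150 to 195 min is time to a result, not length of stay.

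**The case against.** The case against has several parts.

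- **Timing is not stated.** Nothing in the article says that an assessment delays discharge, or where the assessments fall relative to the result, the CT or the disposition. The 15-minute assay wait could by itself hold the 15-minute MACE-2, and the article calls the battery brief. This stands, and it is why the range starts at 0. A reader might infer that study procedures do lengthen the stay most in no-CT patients; the documents make that plausible but do not show it.
- **Size.** A reader might infer that the saving would be hidden, since 25 to 45 min resembles the 45 min mentioned in Preliminary work. That 45 min is the gain from plasma to whole blood, not the contrast with CT. Against 150 to 195 min, even the extreme case removes only part. This stands too: attenuation is supported, concealment is not.
- **Operational detail.** The order of assessments may be set out in the full protocol or site procedures, which are not shown. That is fair. However, the clock and the visit schedule are fixed in this article, and research times that are not logged cannot be reliably recovered later.
- **Consequence.** Only a secondary outcome is affected, the likely error runs against the study's own hypothesis, and the CT-rate endpoint is untouched. All true, and this limits the weight of the point.
- **A different clock is no cure.** Arrival to disposition order would still contain consent and the draw, and would drop time in the ED after the order, which the Discussion cares about. This stands, so that clock belongs in a sensitivity analysis only.

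**Conclusion.** The point holds as a possible attenuation. As described, length of stay includes consent and the enrollment assessments, and no safeguard against delayed departure is stated. If CT patients absorb this time while waiting and no-CT patients do not, the saving is understated. On an assumed total of 25 to 45 min, of which only 15 min is documented, the CT versus no-CT difference is understated by 0 to 45 min and the overall Phase 2 versus Phase 4 difference by at most about 5 to 9 min. The proportion of the saving lost cannot be given, because the article states no expected length-of-stay saving. If the true saving is well below 150 min, the proportion is larger than the percentages above. This is a cheap improvement to a secondary outcome, not a flaw in the primary comparison.

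**What to change.** Keep presentation to discharge as the outcome, and add the following:

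1. Record start and stop times of consent and of the study assessments in REDCap.
2. State that the NSI and knowledge surveys must not delay departure and may be finished remotely the same day.
3. Add two sensitivity analyses: arrival to disposition order, and length of stay net of research time that delayed care. Say in advance which logged minutes count as delay, for example consent before the draw and assessments still running after the disposition order.

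If the full protocol already sequences the assessments so that they do not delay departure, one sentence saying so would cover item 2.

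The cost is two REDCap fields (a second pair if consent and assessments are logged separately), one more timestamp from the record, and a few questionnaires completed just after the visit instead of during it.
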